## Abstract

**Background:**

The use of guidelines in general practice is not optimal. Although evidence-based methods to improve guideline adherence are available, variation in physician adherence to general practice guidelines remains relatively high. The objective for this study is to transfer a quality improvement strategy based on audit, feedback, educational materials, and peer group discussion moderated by local opinion leaders to the field. The research questions are: is the multifaceted strategy implemented on a large scale as planned?; what is the effect on general practitioners' (GPs) test ordering and prescribing behaviour?; and what are the costs of implementing the strategy?

**Methods:**

In order to evaluate the effects, costs and feasibility of this new strategy we plan a multi-centre cluster randomized controlled trial (RCT) with a balanced incomplete block design. Local GP groups in the south of the Netherlands already taking part in pharmacotherapeutic audit meeting groups, will be recruited by regional health officers. Approximately 50 groups of GPs will be randomly allocated to two arms. These GPs will be offered two different balanced sets of clinical topics. Each GP within a group will receive comparative feedback on test ordering and prescribing performance. The feedback will be discussed in the group and working agreements will be created after discussion of the guidelines and barriers to change. The data for the feedback will be collected from existing and newly formed databases, both at baseline and after one year.

**Discussion:**

We are not aware of published studies on successes and failures of attempts to transfer to the stakeholders in the field a multifaceted strategy aimed at GPs' test ordering and prescribing behaviour. This pragmatic study will focus on compatibility with existing infrastructure, while permitting a certain degree of adaptation to local needs and routines.

**Trial registration:**

Nederlands Trial Register ISRCTN40008171

## Background

With the ever-growing volume of evidence from medical research, it has become impossible for physicians to remain fully up to date. Reviews and guidelines therefore summarize large quantities of information, making it more easily available to field workers. In the Netherlands, general practitioners (GPs) now have access to more than 80 evidence-based medical guidelines developed by the Dutch College of General Practitioners (NHG). Although general adherence to these guidelines is approximately 70%, the inter-physician variation is large, and adherence to certain aspects of these guidelines proves to be difficult [1-3]. Although there may be sensible reasons to deviate from guidelines, such as multi-morbidity in a patient, a physician's level of uncertainty tolerance and patients' preferences, there seems to be room for improvement. The inter-physician variation can be regarded as underdiagnosing or undertreating one group of people and at the same time overdiagnosing and overtreating another group, both leading to inappropriate care [4]. There is considerable inter-physician variation in general practice with regard to test ordering and prescribing [5,6].

Many studies have tried to find evidence for effective implementation strategies to improve quality of care. A multifaceted clustered RCT by [name] *et al*. aimed at optimizing GPs' test ordering behaviour by means of local quality improvement collaboratives (LQICs), found a decrease of 8 to 12% in test volumes over a period of six months [7]. This strategy was tested using six topics for continuing medical education (CME). Other studies have tested several implementation strategies to improve test ordering and prescribing behaviour. Passive dissemination of guidelines or recommendations does not seem to influence test ordering behaviour. Audit and feedback have often been used and showed mostly a modest effect in terms of influencing test ordering or prescribing. The effect of audit and feedback on adherence to desired practice ranged from -10% to +68% (median +16%) [8-12]. In other studies, the introduction of a problem-based test ordering form proved to be a promising tool to improve test ordering [7,13-18]. Similar effects on volumes of tests ordered as those in the [name] study have been found for more or less similar multifaceted implementation strategies [19,20]. Small group peer review using direct individual feedback seemed to reduce inappropriate prescribing [12,21,22]. Lagerlov found a 6 to 13% improvement in adherence to guidelines for the prescription of anti-asthmatic drugs and antibiotics for urinary tract infections in an RCT using reflection on guidelines and prescription feedback in small groups [23].

The Cochrane Effective Practice and Organization of Care group (EPOC) systematically reviews studies on implementation strategies to improve quality of care. Their work has generated the general insight that multifaceted strategies are usually more effective than single interventions [12,24], although this was not entirely confirmed by an NHS HTA review by Grimshaw *et al*. [16]. The prevailing insight is that the effect of an intervention is larger when tailored strategies are used and when barriers to and facilitators of change are addressed.

Grol has identified in his model of effective implementation six stages in quality of care improvement[25]. In the first stage, new research findings, new guidelines, experienced weaknesses, or best practices create an opportunity for quality improvement. In the second stage, after the initial implementation process has been planned, targets for improvement or change are set. Prior to the actual implementation, the performance, target group, and setting are analysed. In the fourth stage, the strategies that are to be used are identified and tested. The implementation is developed, tested, and executed. Finally, the implementation is evaluated and adapted, if necessary [25]. The present study will deal with the actual sustainable transfer of a successful implementation strategy to the field. We are not aware of published studies testing this process, or whether effects are sustainable when transferred to the field. Nor are we aware of published studies on the implementation of a large-scale strategy aimed at influencing both the test ordering and prescribing behaviour of GPs simultaneously, using peer review and social influencing in primary care collaboratives.

In the Netherlands, existing networks of pharmacotherapeutic audit meetings (PTAM) can be used to disseminate and implement guidelines on test ordering and prescribing. The goal of setting up these meetings by primary care providers was to improve the quality of their prescribing behaviour [26]. The local groups usually consist of six to ten GPs with affiliated community pharmacists [27]. During the meetings, they discuss the choice of drugs in the context of a specific illness or disease. In recent decades, this form of CME has gained widespread acceptance amongst GPs and policymakers in the Netherlands. However, these sessions tend to offer little or no room for discussions on test ordering. Because no other system of regular meetings exists, the possible underuse, overuse, and misuse of diagnostic services is not discussed by primary care providers on a regular basis.

The Dutch Institute for the Proper Use of Medicine (DGV) supports and initiates local or regional implementation of quality improvement projects on the use of drugs and supports local PTAM groups by supplying them with information and educational materials [28]. Performance levels of PTAM groups are assessed once a year and rated on the basis of four levels, level one being the poorest level of performance and level four the highest. We will use this division into levels as a parameter for pre-randomization stratification.

Participation in PTAM groups by GPs is facilitated by national and regional support organizations for primary care, as well as by the government and through incentives by insurance companies. Attendance at PTAM meetings is rewarded by accreditation. Currently, approximately 50% of the group meetings reach the desired level of performance described by policymakers [27]. To reach this level, groups must at least use feedback on prescribing, create working agreements, discuss barriers to change, and evaluate working agreements. Most groups are stable and remain together for 10 years or more, with members mostly being replaced gradually [27]. Because of the nature and stability of these groups, they provide an excellent and safe environment for participants to discuss their own behaviour and barriers to change. We expect this existing system of PTAM groups will ensure sustainability of the implementation itself. Therefore, we plan to use these groups in a large pragmatic trial on the implementation of guidelines, using the strategy previously tested by [name] *et al*. [7]. However, we will expand the strategy, using social interaction and external influencing as key approaches for establishing behavioural change, to both test ordering and drug prescribing. In our view, the groups will no longer function merely as a PTAM group, but rather begin acting as LQICs. This trial is expected to show whether the effects found in less pragmatic trials can be confirmed. Aiming at both test ordering and drug prescribing, our combination strategy could lead to an even larger effect because of synergy. We will also evaluate the costs of implementing the strategy on a large scale.

## Objectives and research questions

### Hypotheses

We expect that the transfer of the strategy of LQICs to stakeholders in the field will be feasible. We hereby hope to create a solid basis for continuation after the end of the study.

We also expect that large-scale implementation, giving attention to both test ordering and prescribing behaviour, will lead to similar changes in performance as those found on test ordering in the trial by [name] *et al*. [7].

Successful implementation will be positively related to the level of group performance of the groups included, in terms of level of attendance, number of meetings, drawing up working agreements, discussing barriers to change, and evaluating working agreements.

### Objectives

1. To implement the LQIC strategy in the south of the Netherlands, stimulating the relevant parties in the field to take the lead.

2. To determine the critical conditions for effective nationwide implementation.

3. To improve the level of group performance in the participating groups.

4. To reduce undesirable physician variation in test ordering and prescribing; and to reduce underuse or overuse of specific tests and drugs.

5. To examine the costs of large-scale implementation of this strategy, and thus to be able to predict future costs for expansion and maintenance of the strategy.

#### Research questions

##### Process

1. Was the strategy implemented as planned?

2. What were the barriers to and facilitators of the implementation of the strategy?

3. Has the level of group performance been improved in the participating groups?

##### Effect

1. Do the volumes of tests ordered and drugs prescribed change in the preferred direction, as described in the working agreements of the LQICs, compared to baseline?

2. What is the effect of this strategy on GPs' test ordering and prescribing behaviour in terms of interphysician variation and total volumes of tests and prescriptions with respect to specific clinical topics, compared to that among GPs exposed to the same strategy but for other topics?

3. Is any gain in the level of group performance predictive of the effect achieved?

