### Sample size

A sample size calculation is not really possible beforehand, because it is not yet known what working agreements will be created and with respect to what tests or drugs. The specific targets, incorporated in working agreements will probably be based on extreme overuse or underuse of certain tests or drugs by some or all group members. It is possible, for instance, that the group will decide to eliminate a particular obsolete test or drug or create a working agreement to decrease or increase the mean volume of tests ordered or drugs prescribed by 20%, from 35% to 55%.

The sample size calculation used in this trial is as follows: to detect an improvement of 20% in a certain target between groups, assuming an ICC of 0.10 [5], an alpha of 0.05 and a beta of 0.1 and a mean group size of seven, 44 LQICs would be needed. Anticipating a dropout of 10%, we would need to recruit 50 groups. A population this large would account for approximately 900,000 registered patients.

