#### Effect evaluation

1. The volumes of particular tests ordered and particular drugs prescribed for which the group has agreed that change, either decrease or increase, would be necessary.

2. The total volumes of tests ordered and drugs prescribed by the participating GPs for the clinical topics chosen.

3. The inter-physician variation in test ordering and prescribing behaviour for the clinical topics chosen.

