### Measurements

Prior to randomization, the chair of the group will be asked to fill out a short pre-randomization form, with which we will be able to determine the number of GPs in the group and be able to assess the level of group performance [See Additional file 1]. Data on test ordering and prescribing behavior will be extracted from the existing databases at baseline (t = 0) and t = 6 months, t = 12 months and t = 18 months. The dataset obtained at t = 0 and the final set will be used for a before-after analysis. A new questionnaire will be sent to the chair, assessing the level of group performance after the intervention. After each meeting, the chair will be asked to fill out a form with questions about the structure of the session, whether working agreements were created, whether barriers to change were discussed and if so what the nature of these barriers was, what educational materials were used, and the group members' experiences with the strategy.

The process of implementing the strategy in the south of the Netherlands will be monitored. Participants will be questioned about their experiences with the strategy. Participating GPs will be asked to report their experiences with the strategy, and to provide us with the necessary details on the sessions they have attended. After each session, the targets set by each group will be recorded.

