### Analysis

Analysis will be based on the intention-to-treat principle. Data on GPs lost to follow-up will be extracted from the various databases if possible.

We will analyse covariance using test and drug volumes during the intervention period as the dependent variables, and the baseline data and the explanatory variables as independent variables. The analysis will be repeated using proportions stemming from prescription performance indicators, if available. The unit of allocation to the trial is the LQIC. In larger practices with more than one GP, not all volumes of tests ordered and drugs prescribed will be traceable to an individual GP. In these cases, the unit of analysis will be the practice as a whole. Because of this unit of analysis error, the data will be analysed using multilevel modelling. Data on drugs and tests will be clustered to individual GPs at level one, the practice at level two, the LQIC at level three and the region at level four.

The nature of this study makes it difficult to blind the participants, except for the tests or drugs serving as controls in the other arm. The data analyst will be blinded for the allocation result. Costs of the intervention will be calculated. A cost-effectiveness analysis will be based on these figures. We will use cost minimization analysis from a societal perspective, assuming that the strategy will reduce redundant testing and prescribing. If there are signs of improvement of care (higher scores on the performance indicators), the impact on health may be estimated by modelling the future gains and benefits. Data include costs of coordinating the strategy by the regional contact group, of preparing feedback reports and of chairing the GP groups. The costs of the entire test ordering strategy by [name] were €554.70 per GP per six months (three meetings). The major part of the cost of this strategy consisted of opportunity costs, *viz *the costs of the GPs' time spent attending the session. Because GPs were already attending these meetings and were financially compensated, it seems fair to ignore the opportunity costs. This results in costs of the test ordering strategy of €92.70. The gains obtained by improving test ordering behaviour were €301.00 per GP per six months. Introducing the test ordering strategy would save €208.30 (92.70 to 301.00) per GP per six months [33]. Because prescribing costs are higher, the cost reductions gained by reducing superfluous prescribing should also be higher.

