## Discussion

To our knowledge, few studies have been published on the transfer of effective implementation strategies to the field. Our strategy has proved to be effective in an earlier trial on test ordering by GPs in the Netherlands. However, because this strategy was disseminated and controlled by academics, it remains unclear how large its effect will be when transferred to the field. We set up a pragmatic design in order to test this final step in implementation research, giving the diagnostic centres a leading role and leaving GPs much room to adapt and to internalise the strategy. The project team will act as facilitators to these centres, the pharmacists involved, and the LQICs. The strategy is targeted first on test ordering and second on prescribing, which is the natural order followed by GPs when consulted by a patient.

Our strategy is based upon several theories on effective behaviour change and on effective implementation. These theories can be identified at several levels of organisation in our trial. At the level of diagnostic centres and the LQICs, we expect the innovators and early adopters to join the trial, which refers to Roger's innovation-diffusion theory [34]. Within groups we expect to see change according to theories such as Ajzen's theory of planned behaviour and the PDSA-cycles [25,35]. During a meeting, we expect to see the preparation for change based on performance data and actual actions towards change. When new data will be provided to the groups, we expect reflection on the goals previously set. The theory of planned behaviour states that individuals are willing to show change in behaviour dependent on the perceived control over the behaviour itself, the attitude of the individual to the desired behaviour, and the perceived social norms. By providing graphical comparative feedback, we target at these perceived social norms. Comparative feedback sets the norm for a group, and through the phenomenon that one does not like to be an outlier we expect regression to the mean with regard to the inter-physician variation. The moderator who is also an expert on the subject under discussion is expected to act as opinion leader. Furthermore, even a GP from within the group itself can act as a local opinion leader and thus influence the rest of the group.

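### Effect question 1 judges self-chosen, probably extreme targets against each group's own baseline, so regression to the mean and secular trend can look like an effect

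*Protocol article*

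**What the plan says.** The first Effect research question asks whether volumes "change in the preferred direction, as described in the working agreements of the LQICs, compared to baseline". The second concerns total volumes and inter-physician variation by topic, and it names a control: "compared to that among GPs exposed to the same strategy but for other topics". The first outcome under Effect evaluation is the volume of the tests and drugs "for which the group has agreed that change, either decrease or increase, would be necessary". The Sample size section expects that these targets "will probably be based on extreme overuse or underuse of certain tests or drugs by some or all group members". Under Measurements, extracts are taken at 0, 6, 12 and 18 months, and "The dataset obtained at t = 0 and the final set will be used for a before-after analysis".

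Other parts of the article point to a controlled comparison. Design and ethics makes each LQIC a control for the other arm's topics. Sample size plans for a 20% improvement in a target between groups. The Analysis section describes analysis of covariance in a multilevel model with "the baseline data and the explanatory variables as independent variables"; arm is not among the listed terms.

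**The concern.** A group sees its comparative feedback, picks an item on which it stands out, agrees to move it toward the norm, and is then scored on change from its own starting value. A volume that is extreme in one period is partly extreme by chance. The next period will on average lie closer to the mean, whether or not the meeting changed anything. Selection works in the agreed direction for high and low items alike, so the errors do not cancel across groups. Any secular change in use of the item enters the same difference.

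The article mentions the phenomenon once, in the Discussion: "we expect regression to the mean with regard to the inter-physician variation". There it means GPs conforming to a group norm, as a hoped-for result of feedback. It is nowhere treated as a source of bias. At stake is a first-listed effect question that could be answered positively for an ineffective strategy, although the data for a controlled answer are already being collected.

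**Working it through.** **1. The plan's own sizing.** Sample size gives 44 LQICs for 35% against 55%, ICC 0.10, seven GPs per group, alpha 0.05 and beta 0.1. The design effect is 1 + (7 - 1) × 0.10 = 1.6. With two arms, two-sided alpha and 80% power, 96 GPs per arm × 1.6 / 7 = 21.9, so 22 groups per arm and 44 in all. With the stated beta of 0.1 it would be 128 × 1.6 / 7 = 29.3, so 30 per arm and 60 in all. That mismatch is a separate matter. Here the figure shows that 44 is reproduced by a two-arm contrast on a target, which is not the comparison that question 1 names.

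**2. Individual GPs, no intervention effect.** Assumptions, none given in the article: normal volumes, CV 0.3 to 0.5, between-period correlation r, and targets set for GPs more than 1 SD above the mean (about the top 16%, whose mean is +1.525 SD). The expected fall as a share of the selected mean is (1 - r) × 1.525 × CV / (1 + 1.525 × CV).
- CV 0.3: 0.4575 / 1.4575 = 0.314, giving 3.1% at r = 0.9, 6.3% at 0.8 and 9.4% at 0.7.
- CV 0.5: 0.7625 / 1.7625 = 0.433, giving 4.3%, 8.7% and 13.0%.

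**3. Group means selected the same way.** With the article's ICC of 0.10 and seven GPs, the SD of a group mean is √(0.10 + 0.90/7) = 0.478 of the GP SD, so the CV becomes 0.143 to 0.239.
- CV 0.143: 0.219 / 1.219 = 0.179, giving 3.6% at r = 0.8 and 5.4% at 0.7.
- CV 0.239: 0.365 / 1.365 = 0.267, giving 5.3% and 8.0%.

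This takes the same r for group means. If period-to-period noise is independent between GPs, the group correlation is higher and the fall smaller.

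**4. Each group targets its most extreme item.** Null simulation: 50 groups of seven, ICC 0.10, 20 items per topic (204 / 10, rounded), 25 groups each targeting their most extreme item, 200 runs. Cells show the mean own-baseline change in the preferred direction, with the share of runs nominally significant in brackets. The last two columns give the mean difference, in percentage points, after baseline adjustment using the other arm.

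| r | CV 0.3 | CV 0.5 | adjusted, CV 0.3 | adjusted, CV 0.5 |
|---|---|---|---|---|
| 0.9 | 2.2% (48%) | 4.7% (36%) | -0.05 | -0.14 |
| 0.8 | 4.7% (80%) | 10.5% (69%) | 0.22 | 0.04 |
| 0.7 | 6.8% (94%) | 14.9% (90%) | -0.01 | -0.08 |
| 0.6 | 9.5% (99%) | 19.9% (97%) | 0.15 | 0.07 |

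The simulation has no secular trend and takes each item's average as known; only the slope on baseline comes from the other arm. It therefore speaks to regression to the mean alone. The crude test on the adjusted difference rejected in 7 to 12.5% of runs because it ignored the error in that slope. The near-zero bias is the result to use, not that error rate.

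**5. Yardstick.** The Hypotheses section expects changes similar to the earlier test-ordering trial, which the Background puts at 8 to 12%.

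**The case against.** The strongest reply is that the trial is controlled and the article says so. The sample size is for a target between groups, each LQIC is a control for the other arm, and the baseline-adjusted multilevel model is not restricted to question 2. Blinding the analyst to allocation makes sense only if arms are compared. On this reading, the before-after sentence merely names which extracts are used. This stands in part: a reader might infer that the targets have no control at all, and the documents do not support that. What they show is a research question and a measurement rule set against own baseline, beside design text that implies a between-arm contrast, with nothing to reconcile them.

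Four further limits stand.
- Calling this the headline or primary result would go too far. No primary outcome is named, and question 2, which is controlled, is untouched.
- Extreme use is only the probable basis for targets. Sample size also mentions dropping an obsolete test or drug, which need not depend on an extreme volume.
- Topics are handled in sequence and new datasets arrive every six months (Time schedule). Later targets may be chosen on data newer than t = 0, and the formula above does not describe those.
- One might infer a seasonal bias from comparing t = 0 with t = 18 months. The Abstract speaks of data at baseline and after one year, so opposite half-years are not established.

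**Conclusion.** The concern holds, confined to Effect question 1, the first effect outcome and the before-after analysis. As worded, regression to the mean and secular trend can produce change in the preferred direction with no effect of the strategy. Under assumed CV 0.3-0.5 and r 0.7-0.8, regression to the mean alone gives about 6-13% for individual GPs in the top 16% and about 4-8% for group means selected the same way. It is larger if each group targets its most extreme item, and only 3-4% for individual GPs at r = 0.9. It may match the expected 8-12%, but that it will do so does not follow, because the article gives neither CV nor r.

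**What to change.** Restate Effect question 1 and the before-after sentence under Measurements along these lines: *For each test or drug named in a working agreement, follow-up volume in the LQICs that made the agreement will be compared with the volume of the same item in other-arm LQICs over the same calendar window. The planned multilevel model will be used, with arm as a term and adjustment for baseline volume. Change from a group's own baseline will be reported as descriptive only.* Where a later topic was set on a newer six-monthly extract, say which extract serves as baseline.

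No extra pre-period extract and no extremity cut in the control groups are needed, since baseline adjustment using the other arm brought the average bias to about zero. The cost is wording and somewhat more analysis work. Two limits remain. Items shared by topics in both arms give a weaker contrast; the Discussion concedes such overlap for the diabetes and hypercholesterolaemia tests. And only the groups that chose an item contribute on the intervention side, so the comparison leans on the baseline adjustment as well as on randomisation.
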